Active video games, such as Nintendo Wii™ (Nintendo Co., Ltd., Kyoto, Japan) Xbox Kinect (Microsoft Co., Redmond, WA, USA) and Konami Dance Dance Revolution (Harmonix Music Systems Inc., Cambridge, Massachusetts, USA), have become amazingly popular among children and adolescents. For instance, the market best seller, Nintendo Wii™, sold 99 million games consoles in 2012 worldwide [29]. An active video game is one in which playing the game is based on the player’s movements. Thus, these games may provide one possibility for decreasing sedentary screen time and motivating children to be more physically active. The explosive popularity of these games has also inspired physiotherapists and other health professionals to use and study them in rehabilitation [30-32]. Even though these games may not be the solution to achieving the recommended physical activity in healthy children, they might be helpful in breaking up sedentary time in some special circumstances, such as during hospitalization or isolation. These games are also feasible for cancer patients because they can be played in patient rooms, where the risk of infection is minimized. In addition, children are motivated to play them, as they are safe and fun to play [33].

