### Study aims

The primary aim of this study is to evaluate the efficacy of active video games with regard to the promotion of physical activity in children with cancer. The ultimate goal is to motivate children with cancer and their families to integrate active lifestyle choices into their everyday life, even during treatment, to decrease the negative impact of high levels of sedentary behavior. The results will help answer the question of whether playing active video games has a positive effect on the health of children with cancer.

Our hypothesis is that the possibility to play active video games and guidance given to the family about physical activity during cancer treatment promote children’s physical activity and shorten sedentary periods when compared to the control group, who receive only a general recommendation to be active.

The detailed research questions and hypotheses of the study are:

1. Is playing active video games effective in increasing the physical activity of children with cancer during cancer treatment?

a) It is hypothesized that the possibility of playing active video games during cancer treatment promotes children’s physical activity compared to controls.

2. Is playing active video games effective in promoting motor performance during cancer treatment?

b) It is hypothesized that children’s motor performance in the intervention group is maintained better than in the control group.

3. Is playing active video games effective in reducing experienced fatigue by children with cancer?

c) It is hypothesized that the children in the intervention group experience less fatigue during cancer treatment than the children in the control group.

4. Do playing active video games have impact on children’s body mass index and the development of metabolic risk factors in children with cancer?

d) It is hypothesized that playing active video games has a positive impact on children’s body mass index and metabolic risk factors during cancer treatment.

5. What are the children’s and families’ perceptions of the most enjoyed activation methods during cancer treatment?

The protocol follows the methodological guidelines for clinical trials outlined in the CONSORT statement [42].

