### Intervention

The physical activity in the intervention is based on active video gaming. The intervention consists of playing elective active Nintendo Wii™ games daily, for at least 30 minutes, during hospitalization and at home for 8 weeks in total, with consideration of the participants’ individual conditions. Physical activity is not allowed during fever and vomiting or nausea episodes, or if the medical condition changes acutely. The physical activity intensity is recommended as light-to-moderate. One way to monitor the relative intensity of activity is to monitor the respiration and breathing rate during the activity [45]. The parents are guided that light-to-moderate intensity physical activity equals only to slightly increased breathing rate, still feeling “easy to breath” or “slight breathlessness” and they are advised to monitor the child’s condition before and during the physical activities. At the beginning of the study, the attending physician verifies the children’s ability to physical activity, and, if there are significant changes to the child’s condition, the researcher and the physical therapists who conduct the motor performance testing are informed. The children receiving anthracycline therapy are also followed by a cardiologist and regular echocardiograms.

The intervention includes information and recommendations for physical activity and guidance on which Nintendo Wii™ Fit games to play and how to play them. All children in the intervention group will receive the same written instructions and individual face-to-face teaching, where examples about suitable games for each age group are presented. For 3- to 6-year-old children, games such as Hola hoop or Jogging are recommended based on the easiest difficulty levels. For children aged 7- to 10-years, the recommended games include such as Island Cycling, Rhythm Kung-Fu, Hola hoop and Jogging and for 11- to 16-year-old children there are recommended games from all the four types of exercises (aerobics, balance, strength training, yoga). This guidance and instruction are given by a physiotherapist in the hospital. The physiotherapist contacts the participants in the intervention group via telephone for consultation during the intervention in order to encourage children to play and be active. Children in the intervention group have the game console and games at home for the duration of the intervention period.

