The first physical activity questionnaire assesses leisure-time physical activity in metabolic equivalent (MET) hours (METh) per week. The questionnaire contains multiple-choice questions about physical activity intensity, duration and frequency and it is widely used self-reported questionnaire [48]. The questionnaire has previously been used in studies of children’s and adolescents’ physical activity and vascular health [49-51]. The questionnaire correlated relatively well with the accelerometer data (r = 0.26–0.40) and pedometers (r = 0.30–0.39) [50]. For the children under 10 years old, this questionnaire was modified, the parents filling it in as a proxy report of their child. The other activity questionnaire was developed for this study and adds questions about the children’s physical activity and sedentary behavior, such as how much time the children spend in sedentary screen-based activities. The questions are divided into categories: sedentary behavior, light activities, moderate activities and vigorous intensity activities [52]. Report estimates the amount of these activities during a normal day.

The activity diary is completed for one week at every measurement point. The measurement points are: at baseline, 2 months, 6 months, 1 year and 2.5 years after the baseline. Using the activity diary data, we get self- and proxy-reported estimates about the frequency and duration of activity. Behaviors and activities are collected in 10-minute periods 24 hours a day, and the activities that are filled in the diary are divided into categories (sleeping, being awake but lying in bed, being awake and sitting, light activity, moderate activity, vigorous activity or playing active video games). Hence, the child’s acts are collected during the whole 24 hours for seven days in every measurement points. Moreover, the intervention group fills out a special game diary to separate the active videogame playtime and different games they play from other activity. The self- or proxy reported data from the diaries may not be precise but it will give directions and add valuable information to the objectively collected data.

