### Data analysis

The quantitative data from the activity and fatigue questionnaires, M-ABC scores, accelerometers and metabolic risk factors are to be analyzed and tested using statistical methods. Normally-distributed data will be tested for differences between the intervention and control groups by using a two-sample *t*-test and non-normally-distributed data Wilcoxon rank-sum test. Categorical variables will be tested with a chi-squared test. Multivariable analysis will be conducted with potential confounders if the researcher and statistician find it relevant. Statistical software SPSS (IBM SPSS Statistics 21) will be used. The statistical significance will be set at p <0.05.

The activity diaries will be analyzed by counting the continuous length of sedentary periods and the amount of sedentary periods lasting longer than two hours. The activity periods and their lengths will be counted and summarized. These results will be assimilated into the data from the accelerometers and compared between the groups. Activity data will also be surveyed longitudinally over the whole 2.5-year treatment time and reported as descriptive summaries. Game diaries will be analyzed by counting the duration and frequency for the gaming and the games the participants have played the most. The qualitative data from the interviews will be analyzed with content analysis.

The results will be reported following the methodological guidelines for clinical trials outlined in the CONSORT statement [42].

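### The diary count of sedentary periods over two hours can rise when gaming breaks up a very long period, so its group comparison is ambiguous

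*Protocol article*

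**What the plan says.** Sedentary behaviour is one of the two main outcomes (Outcome measurements and time-points of assessments). The hypothesis in Study aims is that the intervention will "shorten sedentary periods when compared to the control group". The Background gives the mechanism for children in hospital or isolation: the games "they might be helpful in breaking up sedentary time in some special circumstances, such as during hospitalization or isolation".

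The Data analysis section names two diary summaries of sedentary behaviour: "counting the continuous length of sedentary periods and the amount of sedentary periods lasting longer than two hours". It continues: "The activity periods and their lengths will be counted and summarized". On use it says: "These results will be assimilated into the data from the accelerometers and compared between the groups".

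Three further details matter:
- The intervention is "playing elective active Nintendo Wii™ games daily, for at least 30 minutes". Whether this is one block is not stated.
- On resolution, "Behaviors and activities are collected in 10-minute periods 24 hours a day".
- The diary categories begin with "sleeping, being awake but lying in bed, being awake and sitting, light activity", and active video gaming has a category of its own. The article does not say which categories count as sedentary.

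**The concern.** The intervention is meant to interrupt long stretches of sitting or lying. A count of periods above a fixed threshold responds to an interruption in one of three ways. It falls if neither remaining part passes the threshold, stays the same if one does, and rises if both do. In the last case a child who has become less sedentary scores worse.

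The count is fixed in the text as a quantity to compare between groups. If some children move up and others down for the same real benefit, the group difference mixes opposite signs. A true reduction could then appear as no difference, or as more prolonged sedentary behaviour in the gaming group. The accelerometer is worn only in the first intervention week and at one year. At two months, when the 8-week intervention ends, evidence on sedentary behaviour therefore comes from the diary and questionnaires.

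**Working it through.** The plan gives no figure for this measure, so there is none to reproduce. Its one power calculation (17 per group) concerns accelerometer counts and does not enter here.

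**Inputs**
- Slot length 10 minutes (Outcome measurements). Longer than two hours therefore means at least 13 slots, or 130 minutes.
- Game of 30 minutes, or 3 slots (Intervention). That it is one block, and not counted as sedentary, is my assumption.

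**Step 1: when can the count rise?** Both remaining parts must be at least 130 min, so the original period must be at least 130 + 30 + 130 = 290 min = 4 h 50. With an assumed break of 10 min the limit is 270 min (4 h 30), and with 60 min it is 320 min (5 h 20).

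**Step 2: one period, 30-minute break at every possible slot.** Let a period have n slots. There are n − 2 possible positions. The number that raise the count is n − 28 (zero if negative). The number that lower it is 28 − n (zero if negative, at most n − 2).

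| Period | Positions | Count rises | Unchanged | Falls |
|---|---|---|---|---|
| 2 h 10 | 11 | 0 | 0 | 11 (100%) |
| 3 h | 16 | 0 | 6 | 10 (62.5%) |
| 4 h | 22 | 0 | 18 | 4 (18%) |
| 4 h 40 | 26 | 0 | 26 | 0 |
| 4 h 50 | 27 | 1 (4%) | 26 | 0 |
| 6 h | 34 | 8 (24%) | 26 | 0 |
| 8 h | 46 | 20 (43%) | 26 | 0 |
| 10 h | 58 | 32 (55%) | 26 | 0 |
| 14 h | 82 | 56 (68%) | 26 | 0 |

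Two examples with the break near the middle:
- 6 h becomes 2 h 40 + 2 h 50. The count goes from 1 to 2 while sedentary time falls from 360 to 330 min.
- 4 h becomes 1 h 40 + 1 h 50. The count goes from 1 to 0, the right direction.

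**Step 3: a whole day.** Assume a 14-hour waking day (84 slots), k other breaks of 10 to 30 min at random times, and one randomly timed 30-minute game, with 10,000 simulated days for each k. The day length and k are assumptions, because the documents give neither.

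| k | Mean count, without → with game | Minutes in periods over 2 h, without → with game |
|---|---|---|
| 0 | 1.00 → 1.68 | 840 → 791 |
| 1 | 1.69 → 2.09 | 802 → 741 |
| 2 | 2.10 → 2.29 | 750 → 683 |
| 3 | 2.31 → 2.36 | 692 → 623 |
| 4 | 2.41 → 2.36 | 634 → 565 |
| 6 | 2.29 → 2.14 | 513 → 451 |

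The first count can be checked by hand: 1 + 56/82 = 1.68. The mean count rises for k = 0 to 2, moves by only 0.05 in either direction at k = 3 and 4, and falls beyond that. Minutes in periods over two hours fall in every row. At k = 3 and 4 they fall by 69 minutes, a change that the count barely registers.

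**The case against.** The strongest objection is that the plan already contains a summary that behaves properly. The hypothesis is about shortening sedentary periods, and period length is listed first in the same sentence. When a period is split, each part is shorter than the original. In the simulation mean period length falls from 840 to 414 min at k = 0 and from 171 to 143 min at k = 4. A reader who sees the count up and lengths down would recognise fragmentation. The count is nowhere called primary. It is one diary summary within a set of four instruments, and the article itself treats diary data as imprecise and supplementary. Children are also at home for part of the intervention, and controls are advised to be active daily, so a day with no break at all is an extreme case.

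Most of this stands, and it limits the point. A reader might infer that the count always moves the wrong way, or that the trial's conclusion on sedentary behaviour rests on it. The documents support neither reading. A rise is impossible for periods up to 4 h 40 with a 30-minute break, and other measures are planned. A reader might also infer that reversal is typical of these children. Eligibility does not select bed-bound or isolated children, and no frequency of long periods is given.

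The objection does not remove the problem. The count is still to be compared between groups, and the text does not say how to read it if it disagrees with the lengths. Average length is not a complete safeguard either. Periods of 180 and 30 min average 105, but if the game replaces the 30-minute one the average becomes 180.

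**Conclusion.** The point holds in a limited form. The over-two-hour count can rise when sedentary time falls, but only where a period of at least 4 h 50 is broken by a 30-minute game into two parts that each exceed two hours. Below that it falls or is unchanged. Its expected sign therefore depends on how sedentary the child was to begin with, and a group difference in the count cannot be interpreted on its own.

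The threshold follows from the diary's slots and one assumed 30-minute block. The day-level figures also rest on the assumed 14-hour day and number of breaks, so the size in this trial cannot be computed. Long periods would be more frequent if lying awake or sleep were counted as sedentary, which the article leaves open. Severity is minor to moderate: an ambiguous companion measure of a main outcome, with a better summary available from the same data.

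**What to change.** In Data analysis, for the between-group comparison, replace the count with:
1. total waking sedentary minutes per day; and
2. minutes per day, or share of waking time, accumulated in sedentary periods longer than two hours.

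Derive both from the existing 10-minute diary, leaving out slots in the sleeping category. Neither total in minutes can rise when sedentary slots are replaced by play. Keep the count as a descriptive figure, reported beside the period lengths.

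The cost is one line of analysis wording and a different sum from the same diary, with no new data, visits or patients.

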### Research ethics

The study protocol received the support of the Joint Commission on Ethics of Hospital district of Southwest Finland (15.5.2012 § 153). The research approvals were obtained from all participating institutions (24.9.2012 K66/12 No 13059 and 21.3.2013 65 § R13030).

After the treating oncologist has verified the eligible criteria for the study, the researcher meets the families and provides them with information about the study. Families are adequately informed before consent is asked from them, and they have time to consider their participation overnight or for longer if needed. They have an opportunity to ask questions before giving their consent. Written informed consent is asked from all participants over 6 years old and oral acceptance from children under 6 years old. Written informed consent is asked from the caregivers of children under 15 years old. The caregivers of children over 15 years old are informed about the child’s decision to participate. According to the Medical Research Act, participation in the study can be withdrawn or cancelled at any time without the need to justify the decision [44].

Publishing the protocol is part of the ethical deliberation, since medical research on vulnerable groups, such as children with cancer, needs to be planned carefully [62].

## Discussion

Physical activity and exercise interventions in children with cancer have shown to be mostly beneficial [19,27,28,63]. Studies concerning active video games have shown that playing these games may have a positive impact on children’s physical activity, energy expenditure and motivation to exercise [31,32]. Furthermore, these games may also be beneficial for rehabilitation purposes for children with limited physical function [30]. However, the evidence in the field is still limited.

The primary aim of this study is to provide knowledge of the use of active video games with regard to the promotion of physical activity in children with cancer during cancer treatment, both in hospital and at home. We are also examining the intervention’s effect on motor performance, fatigue and metabolic risk factors. Furthermore, highlighting the children’s views about activation and motivation methods they have or would have enjoyed is a new dimension for discussions in this field.

The results will provide information about whether playing active video games has a positive effect on the studied health outcomes during cancer treatment in children and whether playing these games promotes the children’s physical activity. The study is providing information about children’s physical activity, motor skills, fatigue and metabolic risk factors. Through this study, it may be possible to promote children’s rehabilitation, wellbeing and quality of life. Thus, this information can be used in planning children’s cancer treatment procedures and rehabilitation. The ultimate purpose of this study is preventive—by motivating and activating children to be physically active, independently, during their treatment may potentially help survivors to adopt a positive attitude towards physical activity and possibly avoid other health risks later in life.

From an ethical point of view, the study procedures do not encumber participants excessively. The most intense setup is for the first week of the intervention when the activity diary is completed and the accelerometer worn. Nevertheless, filling out the diary may also be therapeutic in a hospital setting, where time might feel going slowly.

Some limitations of this study must be mentioned. Participation in the intervention study may cause the Hawthorne effect, leading to unusual behavior and biased results. We have not found a validation study for the Fitbit accelerometer and it has not yet been used widely for research purposes, which weakens the validity of the results. In addition, we recognize that including the accelerometer measure only twice during the study for each participant, according to the existing resources, weakens the study design. However, we have several other instruments to measure the primary outcome to reduce this possible limitation. Furthermore, the study runs over a long time period, which may have the effect of producing dropouts. In addition, the control group is also wearing the accelerometer and this may affect the behavior of the children, as they may become more motivated to be active.

This study also has several strengths. From a methodological point of view, the study protocol is built to provide diverse and reliable information from the phenomenon of interest. Randomization and blinding the physical therapists strengthens the study design. The follow-up throughout cancer treatment makes it possible to achieve valuable knowledge of the children’s activity in the long term.

### Trial status

The trial started recruitment in January 2013 and is estimated to complete its follow-up assessments in 2016.
